#### One-month follow-up visit and three-month phone call

The first follow-up visit is at the outpatient clinic 30 days after the surgery. At that time, the patient is interviewed about recovery from surgery. Patients whose prolonged recovery from surgery requires a stay in a primary care unit will be asked about the length of stay and possible complications after leaving the hospital. Data on possible readmissions and reoperations will be collected. Weights of the patients will be measured, the NRS-2002 score will be calculated, the bioimpedance analysis will be performed and the handgrip strength will be measured. The patients will complete the four-day food diary (Supplementary file 1), exercise questionnaire (Supplementary file 2) and QoL questionnaire [38]. Use of postoperative ONS is inquired from the patients. Blood samples are also taken.

The second follow-up at three months after the surgery, will be performed by phone. Albumin, CRP, CEA, hemoglobin and leucocyte count will be measured in health-care centers on a routine basis and the patients will complete a four-day food diary (Supplementary file 1) and QoL [38] and exercise questionnaire (Supplementary file 2). The patients will be interviewed about possible readmissions, reoperations and complications. The food diary will be checked by phone by a clinical nutritionist.

#### One-, two- and five-year follow-up visits

Patients will have follow-up visits one, two and five years after surgery. As is routine, CEA, hemoglobin and leucocyte count will be measured every three months for two years and then every six months until five years post-operatively. During the one-, two- and five-year follow-up visits, creatinine, albumin and CRP will also be measured. Samples of plasma, serum and whole blood will be stored at -80 °C for later analyses. Weight, BMI and bioimpedance analyses will be performed, the handgrip strength will be measured, and the NRS-2002 score will be calculated at each visit. The WHO classification, the Charlson comorbidity index and smoking habits will be recorded. The patients will also complete the QoL questionnaire [38] and exercise questionnaire (Supplementary file 2) at each time point. All patients will receive a whole-body CT scan one year after the surgery. CT scans monitoring the response to adjuvant chemotherapy will be utilized for analysis of recovery from sarcopenia and its effect on the survival and toxicity of chemotherapy. A colonoscopy will be performed two and five years after the surgery. During colonoscopy biopsy samples of normal looking ascending and descending colon and possible adenomas and tumors will be taken. A suction sample of effluent will be taken from the ascending colon. Additionally, a stool sample will be taken before bowel preparation. During every follow-up visit the patient will be interviewed about recovery, and the complications will be recorded. Data on cancer recurrence and its treatment will be collected.

### Study timeline

Randomization started on April 1, 2019 at the Oulu University Hospital and will last until 318 patients are recruited. Data will be collected until five years post-operatively.

### Statistical analysis

This is a superiority trial. Participants will remain in the groups to which they were originally assigned (intention to treat principal). Additionally, per protocol analyses will be performed as sensitivity analyses. In the per protocol analyses, protocol violation is deemed if a patient consumed < 50% of nutritional drinks in the intervention group or in control group if a patient drank more than 5 nutritional drinks.

All analyses will be adjusted by stratification variable (Nutritional status (NRS 2002) 2, 3–4 or 5). Additionally, the crude outcomes will be reported. The treatment effect will be assessed by odds ratios for categorical data, hazard ratios for survival data and mean differences for continuous data. Random effect models will be used in the case of repeatedly measured data (> 2 repeated measurements). If the incidence of outcome of interest is common (> 10%) then odds ratios will be converted to risk ratios [39].

The treatment effect will be calculated separately for each NRS 2002 stratification class (2, 3–4 and 5). However, as the sample size calculation was performed only for the total treatment effect, the results of the stratified analyses are hypothesis generating only.

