## Methods

### Study setting

This study is accomplished at the Oulu University Hospital, the Kuopio University Hospital, the Seinäjoki Central Hospital and the Rovaniemi Central Hospital in Finland.

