### Sample size

The 30-day complication rates in previous studies [10, 12–17, 23] varied from 8.2 to 77.3% (8.2 to 46.9% for patients receiving ONS, and 12.0 to 77.3% for patients without ONS). Since the sample size of those studies varied from 43 to 432 participants, we calculated weighted 30-day complication rates by using the size of the study as a weight. Accordingly, the weighted 30-day complication rate is 22.0% for patients receiving ONS and 14.9%-unit higher (i.e., 36.9%) for patients without ONS. Further, assuming a two-sided 5% significance level (alfa) and a power of 80% (1-beta) we would need 143 patients per group to show ONS being superior. Accounting for a 10% drop-out rate, the final sample size needed is 159 per group. To recruit this number of patients a 48-month inclusion period was anticipated.

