### Randomization and allocation

Patients undergoing surgery for primary adenocarcinoma of the colon and fulfilling the inclusion criteria will be randomized on their preoperative visit to the outpatient clinic approximately two to three weeks prior to surgery after signing an informed consent form. The patients will be randomly allocated (1:1 ratio) to either an intervention group or a control group according to a computer-generated list compiled by a biostatistician otherwise uninvolved in the clinical care of the trial patients. Allocation will be stratified according to NRS-2002 results (2, 3–4 and 5) and blocked within strata using random permuted blocks (block sizes 2, 4, 6 and 8). A separate randomization list will be created for each participating center. All patients undergoing surgery for colon cancer will be approached and assessed for eligibility and, once their consent is obtained, randomization will be performed. The random allocation will be performed in Case Report Forms (eCRF) where the treatment group cannot be seen before both patient consent and all eligibility criteria fulfilled.

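### Randomisation is restricted by centre and NRS-2002 class, but the analyses adjust for NRS-2002 class only, which makes the tests conservative and costs some power if centres differ

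*Protocol article*

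**What the plan says.** The Randomization and allocation section of the protocol article states: "Allocation will be stratified according to NRS-2002 results (2, 3–4 and 5) and blocked within strata using random permuted blocks". It then adds: "A separate randomization list will be created for each participating center". The Study setting section names four hospitals: "the Oulu University Hospital, the Kuopio University Hospital, the Seinäjoki Central Hospital and the Rovaniemi Central Hospital". Allocation is therefore balanced within 4 × 3 = 12 cells of centre by NRS-2002 class.

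The Statistical analysis section sets the adjustment: "All analyses will be adjusted by stratification variable (Nutritional status (NRS 2002) 2, 3–4 or 5". The variable is singular, and centre appears nowhere in that section. Random effects are reserved for another purpose: "Random effect models will be used in the case of repeatedly measured data (> 2 repeated measurements". The only other analysis mentioned is the crude one, which adjusts for less.

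**The concern.** Separate blocked lists force the arms to be balanced within each hospital, so centre is a stratification factor even though the article does not call it one. When a factor balanced by design also predicts outcome and the model leaves it out, the model-based variance of the treatment effect still contains the between-centre variation that the design has removed. The test then rejects too rarely.

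The article gives some reasons to expect centres to differ. Bowel preparation follows local policy. Unblinded surgeons recruit, treat and collect the data, so recording of complications may vary by site. Three hospitals started in April 2019, November 2019 and April 2021, so centre partly tracks calendar time. Length of stay in institutional care may also depend on local discharge practice, although the article has no figures on this.

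At stake is power on the primary outcome in a trial planned at only 80%.

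**Working it through.** **The plan's own figure.** The Sample size section says "the weighted 30-day complication rate is 22.0% for patients receiving ONS and 14.9%-unit higher (i.e., 36.9%) for patients without ONS" and "assuming a two-sided 5% significance level (alfa) and a power of 80% (1-beta) we would need 143 patients per group". With the unpooled normal formula:

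n = (1.960 + 0.842)² × [0.22 × 0.78 + 0.369 × 0.631] / 0.149² = 142.98, so 143 per group. Then 143 / 0.9 = 158.9, so 159 per group.

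Both stated figures reproduce.

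**Simulation.** Inputs from the article: 2 × 143 = 286 evaluable patients, four centres, three NRS classes, permuted blocks of 2, 4, 6 and 8 within each centre-by-class cell, marginal rates of 36.9% and 22.0%, and two-sided 5%. The outcome is treated as binary, as in the sample size calculation.

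Assumptions, because the article gives no figures: centre shares 45/25/20/10%, NRS class shares 45/45/10%, NRS effects of −0.3, 0.2 and 0.6 on the logit scale, and the between-centre SD on the logit scale. There were 4,000 trials per scenario. Logistic models with and without centre were fitted to the same simulated trials and compared by Wald test.

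| Centre SD (logit) | Control-arm centre rates | Type I error: NRS only / NRS + centre | Power: NRS only / NRS + centre |
|---|---|---|---|
| 0 | 37% in all | 5.1% / 5.4% | 79.7% / 79.8% |
| 0.3 | 31% to 51% | 4.7% / 5.0% | 80.6% / 81.4% |
| 0.5 | 27% to 60% | 4.5% / 5.1% | 81.1% / 82.9% |
| 0.8 | 21% to 73% | 3.1% / 4.6% | 80.4% / 84.5% |

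Monte Carlo error is about 0.35 points for type I error and 0.6 points for power. Taken singly, the 4.7% and 4.5% are within about 1.5 Monte Carlo errors of 5%; the 3.1% is clearly below it.

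The mechanism shows in the standard errors. At SD 0.8 with no treatment effect, the NRS-only model reports a mean SE of 0.249 while the estimates actually vary with an SD of 0.231, so the SE is 0.249 / 0.231 = 1.08 times too large.

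**Interval width on the odds-ratio scale.** With the planned treatment effect, adding centre raises the mean model SE of the log odds ratio from 0.272 to 0.277 (SD 0.3), 0.272 to 0.282 (SD 0.5) and 0.271 to 0.296 (SD 0.8). The odds ratio is non-collapsible: the centre-adjusted odds ratio lies further from 1 and its SE is larger, yet the test gains power.

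**Interval width on a linear scale.** For a mean difference, or a risk difference from a linear model, the omitted factor inflates the SE by 1/√(1 − R²). For a binary outcome R² = between-centre variance / [p̄(1 − p̄)], and type I error = 2 × [1 − Φ(1.96/√(1 − R²))]. With four equal centres and assumed rates:

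- 30/35/40/42%: R² = 0.00217 / 0.2324 = 0.009; interval 0.5% too wide; type I error 4.9%.
- 20/30/40/50%: R² = 0.0125 / 0.2275 = 0.055; interval 2.9% too wide; type I error 4.4%.
- 15/30/45/55%: R² = 0.0230 / 0.2311 = 0.099; interval 5.4% too wide; type I error 3.9%.

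The corresponding power with adjustment, starting from 80%, is 80%, 82% and 84%.

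**The case against.** The strongest reply is that the omission is safe and probably small. The NRS-only analysis errs on the conservative side, so it cannot produce a false-positive conclusion. All sites follow the ERAS protocol with common perioperative care and only bowel preparation left to local policy, so a large spread in complication rates is not to be expected. If centres do not differ, nothing is lost. A second simulation, with equal centres, no NRS effect and 1,500 trials per scenario, used the three sets of rates above, shifted so that the arms average 36.9% and 22.0%. Power moved only from 78% to 78%, 80% to 81% and 81% to 83%, with Monte Carlo error of about 1 point. All of this stands, and it limits the size of the point.

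A further objection also stands: centre terms in every model can be too much. As an illustration, applying the mortality rates quoted in the Background (1.6% and 8%) to 318 patients gives about 5 to 25 deaths. A model with treatment, two NRS terms and three centre terms would then be unstable.

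What does not stand is that the matter is left to a fuller analysis plan. The article itself fixes the adjustment set, for all analyses.

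Three stronger readings are tempting, and the documents do not support them:

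- *The treatment comparison is biased or false positives are inflated.* Randomisation balances the arms within centre, and the error runs the other way.
- *The reported odds ratios will have over-wide intervals that adjustment would narrow.* That holds for mean differences and marginal risk scales. On the log-odds scale the adjusted SE is slightly larger. The article converts odds ratios to risk ratios for common outcomes, but that conversion starts from the odds ratio, so narrowing cannot be taken for granted there either.
- *The sample size is wrong.* It reproduces and does not depend on this point.

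**Conclusion.** The mismatch between design and analysis is certain from the text. Its consequence is a conservative test with some loss of power, and only to the extent that outcomes differ between centres. For modest differences (logit SD 0.3 to 0.5) the loss is about 1 to 2 power points, with type I error of 4.5% to 4.7%. At SD 0.8, which needs control-arm rates from about 21% to 73%, it is about 4 points and 3.1%. With no differences it is nil. These sizes rest on assumed centre rates and shares, so only the direction can be stated with confidence. The point is modest, but it is worth settling before the data are seen, because adding centre afterwards would look data-driven.

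**What to change.** Replace the adjustment sentence in the Statistical analysis section with wording such as:

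> Primary and secondary analyses will be adjusted for both randomisation factors, NRS-2002 class (2, 3–4, 5) and centre. Centre will be a fixed effect in logistic and linear models and a stratum in Cox models. Where a centre or the event count is sparse (for example 90-day mortality, or analyses within an NRS class), a random intercept for centre, pooling of small centres or a reduced model will be used, by a rule set before the data are examined.

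The crude results can still be reported as planned. The cost is three degrees of freedom among 286 evaluable to 318 randomised patients. No new data are needed, and the 143 and 159 per group are unchanged. Adjusting further for age and ASA class is optional and not part of this correction.

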The surgical specimen will all be analyzed by a pathologist, and study pathologists will review the cancer type, grade and classification of malignant tumors (pTNMs) according to TNM8. In addition, the degree of inflammatory reaction at the tumor margin will be recorded using the Klintrup-Mäkinen score [36], and the number of lymphoid structures will be measured according to Väyrynen et al.’s method [37]. The number of intraepithelial lymphocytes and the SMI status will be recorded. The amount of tissue necrosis will be recorded [37]. Samples of subcutaneous and visceral fat tissue, rectus abdominis muscle, liver, tumor, healthy-looking bowel wall (including all layers), peritumoral bowel wall and stool samples will be collected during the operation. Samples will be taken for histological and biochemical analyses. In right-sided cancers, a sample from the terminal ileum will also be taken. The sample´s warm and cold ischemia times will be recorded.

A RAND-36 quality of life questionnaire and an exercise questionnaire (Supplementary file 2) will be completed at every time point [38].

Data about preoperative blood transfusions, oral iron use or intravenous iron infusions will be collected. Operation data will also be collected: operation code, duration, blood loss, infused units of red cells, infused amounts of crystalloids and colloids, bowel preparation before the operation, peroral and intravenous antibiotic use, vasopressor use during the operation, operating surgeon, anastomosis technique, stoma use, operation type and intraoperative complications.

Complications after the primary operation will be collected. Data concerning the length of stay in intensive care and total length of stay in hospital and discharge to home or institution will be collected. The date of first flatus, first passage of stool, use of ONS during hospital stay and ambulatory capacity during hospital discharge will be collected.

Complication data after the primary operation and after possible reoperations will be collected at every follow-up time point. The comprehensive complication index (CCI) will be analyzed. Registered complications include wound, respiratory, cardiovascular, gastrointestinal, anastomosis leakage, urogenital and renal, thromboembolic complications and other infections. The Clavien-Dindo classification will be determined for every complication.

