#### First meeting and the operation

All patients attending this study will visit the outpatient clinic two to three weeks prior to the surgery. In the first meeting, patients are randomized by NRS-2002 as described. Bioimpedance and handgrip strength are measured. Laboratory tests, colonoscopy and CT scan results are registered. Patients will fill out a QoL questionnaire [38] and an exercise questionnaire (Supplementary file 2). Salivary samples are taken. A food diary (Supplementary file 1) is given to patients, and patients will return it when they present for their operation. The food diary will be checked upon return by a clinical nutritionist. All patients are given cancer patient nutrition guidelines. On arrival at the operation, BMI and handgrip strength will be measured. Data on patients’ ONS intake will be collected.

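### The analysis section names NRS-2002 class as the only adjuster and does not secure use of each continuous outcome's own baseline value, which could cost precision on secondary comparisons

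*Protocol article*

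**What the plan says.** The Statistical analysis section says that all analyses are adjusted for the stratification variable, NRS-2002 class (2, 3–4 or 5), and that crude outcomes are also reported. No other covariate is named, and none is ruled out. The effect measure for continuous outcomes is "mean differences for continuous data", without saying whether this means follow-up values, changes or baseline-adjusted values. For outcomes measured repeatedly: "Random effect models will be used in the case of repeatedly measured data (> 2 repeated measurements").

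The baseline data exist. Under Data collection, "A RAND-36 quality of life questionnaire and an exercise questionnaire (Supplementary file 2) will be completed at every time point". Table 2 schedules:

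- quality of life at the first meeting, 30 days, 3 months, and 1, 2 and 5 years;
- grip strength at the first meeting, operation, 30 days, and 1, 2 and 5 years;
- bioimpedance at the first meeting, 30 days, and 1, 2 and 5 years;
- CT at the first meeting and 1 year.

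Quality of life is a listed secondary outcome. Grip strength and body composition are not on that list, but they bear on the secondary aim of improving nutritional status.

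On the baseline visit, the section on the first meeting and the operation reads: "In the first meeting, patients are randomized by NRS-2002 as described. Bioimpedance and handgrip strength are measured". The quality-of-life questionnaire follows in the same paragraph. The trial is open label.

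**The concern.** A patient's own earlier value is usually a strong predictor of the later one, often stronger than a three-level risk class. If follow-up means are compared with adjustment for NRS class alone, between-patient variation that the baseline could explain stays in the error term. Chance baseline differences between arms then carry into the follow-up difference. The confidence interval allows for this, so the cost is width and not validity.

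The sample size was set for complications, so precision on quality of life and nutritional status depends on the analysis. The adjustment sentence covers all analyses, so an analyst who follows the text literally would fit NRS class and stop there.

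The gain also requires a baseline that allocation cannot have influenced. In an open-label trial that matters for a self-reported questionnaire and for an effort-dependent grip test.

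**Working it through.** **The plan's own figure.** The Sample size section gives "the weighted 30-day complication rate is 22.0% for patients receiving ONS" and "14.9%-unit higher (i.e., 36.9%) for patients without ONS", "assuming a two-sided 5% significance level (alfa) and a power of 80% (1-beta"). With unpooled variance:

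n = (0.22 × 0.78 + 0.369 × 0.631) × (1.960 + 0.842)² / 0.149² = 0.4044 × 7.849 / 0.02220 = 142.98, or 143 per group.

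This agrees with "we would need 143 patients per group to show ONS being superior", and 143 / 0.90 gives 159. Nothing below changes these figures.

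**Gain at a single follow-up time.** The documents give neither a baseline-to-follow-up correlation (ρ) nor an SD, so ρ is assumed over a range and effects are in SD units. I assume 143 evaluable patients per arm.

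- Variance of the mean difference, follow-up values only: 2/143, SE 0.118 SD.
- With baseline as covariate: multiply the variance by 1 − ρ².
- With change scores: multiply the variance by 2(1 − ρ).
- Difference detectable with 80% power, follow-up only: 2.802 × 0.118 = 0.331 SD. With baseline adjustment, multiply by √(1 − ρ²).

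| Assumed ρ | 1 − ρ² | Variance cut | CI narrower by | Detectable difference (SD) | Equivalent n per arm | Change-score factor |
|---|---|---|---|---|---|---|
| 0.3 | 0.91 | 9% | 5% | 0.316 | 157 | 1.40 |
| 0.5 | 0.75 | 25% | 13% | 0.287 | 191 | 1.00 |
| 0.7 | 0.51 | 49% | 29% | 0.237 | 280 | 0.60 |

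**Allowing for NRS class already in the model.** Suppose NRS class explains 10% of the variance of both baseline and outcome (assumed). The partial correlation is (ρ − 0.10)/0.90.

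- ρ = 0.5: 0.444, factor 1 − 0.444² = 0.80, a cut of 20%.
- ρ = 0.7: 0.667, factor 0.56, a cut of 44%.

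**Does a random-effects model already deliver the gain?** It depends on its form. A small simulation (ρ = 0.6, baseline plus two follow-ups, 143 per arm, 150 runs) gave these SDs of the treatment estimate at the first follow-up. The last column is the closed-form value for the corresponding single-time analysis, where one was calculated.

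| Model | Simulated SD | Closed form |
|---|---|---|
| Follow-up values only | 0.118 | √(2/143) = 0.118 |
| Baseline as an outcome row, separate baseline means, treatment-by-time effect | 0.113 | √(2/143 × 0.80) = 0.106 |
| Baseline as an outcome row, common baseline mean | 0.100 | – |
| Baseline as covariate | 0.100 | √(2/143 × 0.64) = 0.095 |

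With 150 runs, each SD carries a relative error of about 1/√300 = 6%. The ordering agrees with the closed forms. The plan's sentence fits any of the first three rows.

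**Which outcomes fall under which rule.** Quality of life (six scheduled times), grip strength (six) and bioimpedance (five) exceed two measurements and go to random-effects models. CT has two scheduled scans, baseline included, so the rule does not reach it. What remains for CT is a mean difference adjusted for NRS class.

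**Order of steps.** The Randomization and allocation section hides the arm until consent is given and eligibility is met. NRS score, BMI and albumin are eligibility items, and metastatic disease is an exclusion, so these values and the staging CT should precede allocation. RAND-36, grip strength and bioimpedance are not eligibility items, so that safeguard does not require them beforehand.

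**The case against.** The strongest reply is that the text says adjusted by NRS class, not by NRS class alone, and that a condensed article may leave the handling of baseline to an analysis plan that is not shown. A reader might infer that the trial will discard its baseline data. The documents do not support that: no covariate is excluded, and a random-effects model with a common baseline mean performs as well as baseline adjustment (0.100 against 0.100). This part of the reply stands. What remains is that the article does state an adjustment set for all analyses, leaves baseline out of it, and is equally compatible with models that lose precision.

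A reader might also infer that baseline measurements are taken after randomisation, because the paragraph mentions randomisation first. It lists the contents of one visit without sequence words. NRS scoring, which must precede stratified allocation, has no step of its own there, and the CT results needed for eligibility are listed later. So the order is unstated, not shown to be wrong.

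The size of the gain is also open to challenge. The correlation is assumed, the gain is small at 0.3, and the percentages compare with a follow-up-only analysis. Against change scores the benefit at ρ = 0.7 is only 0.51 against 0.60. These limits stand.

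Finally, adjusting for a baseline taken with the arm known would not be a free gain. That is why the order of steps belongs with the fix.

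**Conclusion.** The point holds as one of efficiency and clarity. NRS class is the only adjuster named, and use of the outcome's own baseline is not secured. Relative to an NRS-adjusted follow-up-only comparison, the variance that could be saved is about 9% to 49% for assumed correlations of 0.3 to 0.7, or 20% and 44% at 0.5 and 0.7 if NRS class already explains 10% of the variance. The case is clearest for CT body composition. For quality of life, grip strength and bioimpedance, any loss depends on how baseline enters the model. There is no evidence of bias, and the primary complication outcome and the total of 318 are untouched. Confidence is moderate, because the correlation is assumed and an analysis plan not shown may already settle the matter.

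**What to change.** In Statistical analysis, state that each continuous outcome with a pre-randomisation measurement is adjusted for that value in addition to NRS-2002 class. Alternatively, for outcomes analysed by random-effects models, state that baseline enters as an outcome row with a mean common to both arms. Say explicitly that CT body composition, with two scheduled scans, takes the first form. Grip strength measured on arrival for surgery falls after preoperative supplementation has begun and should not serve as baseline.

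In the section on the first meeting, state that RAND-36, grip strength and bioimpedance are completed before allocation is opened in the eCRF. This can apply only to patients still to be enrolled; for those already randomised, the order can only be reported as far as the records show it.

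The cost is two sentences and, for future patients, a fixed order of steps within the same visit. No extra patients, visits or measurements are needed.

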### Outcomes

#### Primary outcome

The primary outcome is the number of complications during the 30-day period postoperatively.

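### The 10% rule for converting odds ratios to risk ratios lets observed incidence choose the reported scale and, under the usual formula, gives a miscalibrated interval that is not for the marginal risk ratio

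*Protocol article*

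**What the plan says.** Three sentences in the Statistical analysis section of the protocol article combine. The effect measures are set first: "The treatment effect will be assessed by odds ratios for categorical data, hazard ratios for survival data and mean differences for continuous data". Adjustment is general: "All analyses will be adjusted by stratification variable (Nutritional status (NRS 2002) 2, 3–4 or 5"), with unadjusted results as a supplement: "Additionally, the crude outcomes will be reported". Then comes the rule at issue: "If the incidence of outcome of interest is common (> 10%) then odds ratios will be converted to risk ratios [39"]. The section gives no conversion formula and no method for the confidence limits. It does not say whether the 10% refers to the control arm, either arm or all patients.

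The Sample size section treats the primary outcome as a proportion: "the weighted 30-day complication rate is 22.0% for patients receiving ONS and 14.9%-unit higher (i.e., 36.9%) for patients without ONS". It also gives the spread of the rates behind these averages: "8.2 to 46.9% for patients receiving ONS, and 12.0 to 77.3% for patients without ONS". The Primary outcome section uses other words: "The primary outcome is the number of complications during the 30-day period postoperatively". Because the trial is sized on a proportion and the analysis section names no measure for counts, the odds-ratio route is the only listed one that fits the outcome as sized.

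**The concern.** This is a stated analysis rule, so it can be judged as written. It raises three issues.

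- **Scale chosen by the data.** Whether a result appears as an odds ratio or a risk ratio depends on an observed incidence, and the article does not say which one.
- **Interval.** In ordinary use, converting an odds ratio means passing the estimate and its limits through a formula that contains one baseline risk. That risk is itself estimated from the trial. Treating it as known gives limits of the wrong width.
- **Target.** An odds ratio adjusted for NRS class is conditional on class. Combined with one crude baseline risk, it does not return the risk ratio for the trial population unless class has no bearing on risk.

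At stake is how precisely and how clearly the headline effect is reported. Whether superiority is declared is not at stake.

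**Working it through.** **Inputs from the protocol article.** Risks P1 = 0.220 (ONS) and P0 = 0.369 (control); two-sided 5%; 80% power; 143 per group, 159 after 10% drop-out (Sample size); adjustment for NRS class 2, 3–4, 5 (Statistical analysis).

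**Assumptions, not in the article.** The conversion is RR = OR / (1 − P0 + P0·OR), applied to the estimate and both limits, with P0 the observed control risk. Class shares and class effects are stated where used.

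**1. The plan's own figure.** n = (1.960 + 0.842)² × (0.22×0.78 + 0.369×0.631) / 0.149² = 142.98, so 143 per group. 143 / 0.90 = 158.9, so 159. Both reproduce.

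**2. Will the rule apply?** An observed rate of 10% or less means at most 14 of 143 in an arm.

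| True rate | Probability of observing 10% or less |
|---|---|
| Control 36.9% | about 1.5 × 10⁻¹³ |
| ONS 22.0% | about 0.0001 |
| Control 12.0% (low end of cited range) | 0.25 |
| Both arms pooled, (8.2 + 12.0)/2 = 10.1%, at most 28 of 286 (pairing assumed) | 0.48 |

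At the planning rates the rule is practically certain to apply. At the low end of the article's own ranges it is close to a coin toss, and the answer depends on whose incidence is meant.

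**3. The interval, unadjusted, 143 per arm.**
- OR = (0.22/0.78) / (0.369/0.631) = 0.482; SE(log OR) = 0.266; 95% limits 0.286 to 0.812.
- Converted: 0.482 / (0.631 + 0.369×0.482) = 0.596, limits 0.389 to 0.873.
- Direct: RR = 0.22/0.369 = 0.596; SE(log RR) = 0.192; limits 0.409 to 0.868.
- Width ratio on the log scale: ln(0.873/0.389) / ln(0.868/0.409) = 1.077, about 8% too wide.

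The reason: with P0 held fixed, the slope of log RR on log OR is 1 − P1, so the converted standard error is about (1 − P1) × SE(log OR). At the planning rates that is 0.78 × 0.266 = 0.208 against 0.192, a ratio of 1.08. With the risks reversed it is 0.631 × 0.266 = 0.168 against 0.192, a ratio of 0.88.

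Simulated coverage of nominal 95% intervals (the direct interval covers about 95% throughout):

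| ONS vs control | Converted interval |
|---|---|
| 22.0% vs 36.9% (planned benefit) | 96.8% |
| 36.9% vs 36.9% (no effect) | about 95% |
| 26% vs 22%, or 40% vs 36.9% (small harm) | about 94.5% |
| 45% vs 36.9% | 93.2% |
| 36.9% vs 22.0% (full effect reversed) | about 91.5% |

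In the last row the converted result is 1.68 (1.17 to 2.26) and the direct one 1.68 (1.15 to 2.44), so the converted interval is about 13% too narrow.

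**4. The target after adjustment.** With a true marginal RR of 0.596 and assumed class shares of 50/40/10% or 35/45/20%:

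| Log-odds step per NRS class | Converted RR | Difference |
|---|---|---|
| 0 | 0.596 | 0% |
| 0.5 | 0.587 to 0.588 | −1.4 to −1.6% |
| 0.9 | 0.566 to 0.569 | −4.5 to −5.0% |

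Across these settings, at the planned effect, converted intervals cover 96.2 to 96.9% and are 8 to 19% wider than those from standardising the logistic model, which cover 94.8 to 95.5%. A separate example uses class shares 30/55/15%, control risks 20/42/55% and a common OR of 0.48. The marginal risks are 0.3735 and 0.2295, so RR = 0.614, while the conversion gives 0.48 / (0.6265 + 0.3735×0.48) = 0.596, which is 3% lower.

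**The case against.** The strongest objection is that the article states neither a formula nor an interval method, and its reference for the conversion is not at hand. Risk ratios can be obtained from a logistic model by standardisation with valid limits, and a fuller plan may say so. A reader might infer that the confidence limits are simply wrong; the article does not support that without the closed-form assumption. This part of the objection stands, and the interval and target results are conditional for that reason. It does not rescue the 10% switch, which is written down.

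A reader might also infer that the rule will always be triggered. That fails at the low end of the cited ranges, and it presumes a binary outcome although the Primary outcome section speaks of a number of complications.

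Third, the conclusion of the trial does not change. The assumed conversion is monotone and maps 1 to 1, so the converted interval excludes 1 exactly when the odds-ratio interval does. Type I error and power are untouched. This stands in full. It also tempers the harm argument: the 91.5% figure needs the whole design effect reversed, and small harms cost about half a percentage point of coverage. At the planned effect the error is modest and on the conservative side, and the unadjusted point estimate is exact.

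Finally, sizing a trial on a difference of two proportions does not oblige it to make the risk difference primary, and the difference can be read from crude arm-level risks. That stands too. Making it primary, or adding centre to the model, would be a matter of preference and is not part of this point.

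**Conclusion.** The point holds in limited form. Two things rest on the text alone: the reported scale depends on an observed incidence that is not defined, and at the planning rates the conversion will almost certainly produce the primary effect estimate if the outcome is analysed as the proportion it was sized on.

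The rest assumes the closed-form conversion of estimate and limits. On that assumption the limits are miscalibrated in a direction that depends on the effect: somewhat too wide under benefit, about right at no effect, too narrow under harm. The adjusted value departs from the marginal risk ratio by about 0 to 5%, using class shares and class effects that the article does not give. The Background section cites complication rates of 62% vs 39.8% by nutritional risk in newly diagnosed colon cancer patients, so a prognostic NRS class is plausible, but its strength here is unknown.

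Confidence is medium and priority modest. The case for acting is that a better-defined estimate is available at almost no cost.

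**What to change.** In the Statistical analysis section, delete the 10% switch. For every binary outcome with enough events, prespecify one NRS-adjusted risk ratio, estimated directly, with the risk difference reported alongside. Both can come from standardising the logistic model over the trial population, with delta-method or bootstrap limits. Poisson regression with robust variance is an acceptable alternative for the risk ratio. State that the target is the marginal risk ratio, and that the primary outcome in this analysis is the proportion of patients with a complication, if that is what is meant. The odds ratio may stay as a supplementary result.

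The cost is a few lines of text and standard software. No extra data, patients or visits are needed, and the sample size is unchanged.
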